#### **8.2.2.2 Isolation of Shed Influenza Virus in Chicken Embryos**

Nasal swab specimens will be tested for presence of shed influenza virus by inoculation into 10-day old chicken embryos. Three passages in eggs will be performed – initial passage with nasal swab specimens and two blind passages if necessary. Positive samples will be tested for their infection titre in eggs. These assays will be conducted by IEM.

For these assays, nasal swab specimens collected on Days 1, 2, 3, 5, 7, 29 and 31 will be utilized.

Virus isolated from chicken embryos will be amplified by polymerase chain reaction (PCR) and sequenced in order to determine whether attenuation mutations have been maintained. These procedures will also be conducted by IEM.

#### **Virological assays**

Collection of nasal swab specimens will be performed with sterile dry applicators (COPAN Diagnostics, Inc.) using standard procedure in accordance with MG 4.2.2136-06. Following

collection of the material the applicator will be placed into the sterile tube containing transport medium (COPAN).

Virus isolation will be performed in accordance with the WHO manual on animal influenza, 2002). Normally developing 10-11-day-old chicken embryos (Bred Livestock Farm Ltd. "Nasia", Leningrad Region) will be used. Embryos will be inoculated through allantoic cavity route (each specimen applied for 3 embryos) and incubated for 3 days at temperature 32-34°C. The HA positive allantoic fluid with 1% chicken erythrocytes will be further used for typing and sequencing of the virus isolate obtained. In case of negative HA results, blind passage will be performed (3 days incubation at temperature 32- 34°C). When getting negative results the second blind passage will be performed and after that the sample will be evaluated as negative.

Testing of clinical specimens (nasal and conjunctival swabs) will be done by real-time RT-PCR (Rotor-Gene 6000, Australia) using AmpliSense reagent kit for influenza A virus DNA amplification, and by real-time PCR with hybridization fluorescent detection - INFLUENZA Test-System for PCR Detection and Differentiation of Avian Influenza Virus (the Federal Central Research Institute of Epidemiology under Ministry of Public Health of Russia), for identification of influenza A virus H5, H7 and H9 subtypes in biological material.

#### **8.2.2.3 Mucosal Anti-influenza IgA**

Nasal wick specimens will be tested by quantitative EIA for the presence of anti-influenza IgA according to the CDC protocol (Centers for Disease Control and Prevention, Atlanta, USA).. These assays will be conducted by IEM.

For EIA procedure the following will be used:

1. Antigen – 16 HAU of the vaccine strain A/17/Mallard/ Netherlands/00/95 (H7N3);
2. Phosphate buffer solution (PBS) ("Biolot", Russia);
3. TMB-substrate («BD bioscience», USA)
4. Tween-20 ("Biolot", Russia);
5. Bovine serum albumin (BSA, fraction V) ("Biolot", Russia);
6. Horseradish peroxidase-conjugated rabbit affinity purified anti-human IgA antibodies (Sigma, CША);
7. Disposable EIA polystyrene plates («Medpolymer», Russia).

Vaccine immunogenicity will be evaluated due to the following criteria:

1. Changes in serum IgG and secretory IgA geometric mean titers (GMT) pre- and post- vaccination;
2. Determination of proportions of subjects with antibody response (seroconversions) (4-fold and greater increase in influenza antibody titer).

For these assays, nasal wick specimen collection will occur on Days 0, 28, and 56. Collection must occur at least one hour prior to administration of study vaccine or placebo on Days 0 and 28.

#### 8.2.2.4 Serum Anti-influenza IgA and IgG

Serum specimens will be tested for the presence of anti-influenza IgA and IgG using quantitative EIA according to the CDC protocol (Centers for Disease Control and Prevention, Atlanta, USA). These assays will be conducted by IEM.

For EIA procedure the following will be used:

1. Antigen - 16 HAU of the vaccine strain A/17/Mallard/ Netherlands/00/95 (H7N3);
2. Phosphate buffer solution (PBS) ("Biolot", Russia);
3. TMB-substrate («BD bioscience», USA)
4. Tween-20 ("Biolot", Russia);
5. Bovine serum albumin (BSA, fraction V) ("Biolot", Russia);
6. Horseradish peroxidase-conjugated rabbit affinity purified anti-human IgA antibodies (Sigma, CША);
7. Disposable EIA polystyrene plates («Medpolymer», Russia).

Vaccine immunogenicity will be evaluated due to the following criteria:

1. Changes in serum IgG and secretory IgA geometric mean titers (GMT) pre- and post- vaccination;
2. Determination of proportions of subjects with antibody response (seroconversions) (4-fold and greater increase in influenza antibody titer).

For these assays, serum specimen collection will occur on Days 0, 28 and 56. Collection must prior to administration of study vaccine or placebo on Days 0 and 28.

#### 8.2.2.5 Serum Antibody to Influenza Virus Detected by HAI

The HAI assay is the most frequently used serologic test for determining immunologic response to influenza vaccination. Briefly, sera are pretreated with heat and receptor-destroying enzyme to reduce non-specific inhibition. In 96-well microtiter plates, serum specimens are then serially diluted with doubling dilutions and incubated with standardized titers of influenza virus antigens representing vaccine strains. After incubation, chicken- or human-derived red blood cells are added to individual wells and allowed to sediment. Plates are tipped, and RBCs that have settled will produce a streak (RBCs run or flow), indicating inhibition of hemagglutination and the presence of serum antibodies against the influenza test strain. Wells with lattice formation (hemagglutination) will not streak. When processing paired sera (pre- and post-vaccination), an increase in antibody titer indicates response to vaccination. Serum specimens will be tested for the presence of HAI antibodies to influenza by IEM. Determination of specific anti-influenza antibodies using hemagglutination inhibition test (HI) test will be performed by IEM in accordance with the conventional technique (MG 3.3.2.1758-03. Methods to determine quality characteristics of immunobiological preparations for influenza prevention).

For HI test procedure the following will be used:

1. Antigen - 4 HAU of the vaccine strain A/17/Mallard/ Netherlands/00/95 (H7N3);

2. Human erythrocytes 0(I) Rh+ from erythrocyte concentrates unsuitable for transfusion and acquired in the Municipal blood transfusion station under St.-Petersburg Health Department;
3. Phosphate buffer solution (PBS) ("Biolot", Russia);
4. Disposable polystyrene plates for immunological assays («Medpolymer», Russia).

Vaccine immunogenicity will be evaluated due to the following criteria:

1. Seroconversion factor – increase of antibody geometric mean titers (GMT) on Day 21 in comparison with initial antibody levels in terms of "fold" increase.
2. Seroconversion level – percent of volunteers showing higher than 4-fold increase of antibody titer in comparison with initial values.
3. Seroprotection level – percent of volunteers showing antibody titer exceeding 1:40 on Day 21 post-vaccination.

For these assays, serum specimen collection will occur on Days 0, 28 and 56. Collection must prior to administration of study vaccine or placebo on Days 0 and 28.

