The World Health Organization (WHO) acknowledged advantages of LAIV use compared to inactivated vaccine in case of pandemic events. The main goal stated by WHO in the Global Influenza Preparedness Plan was to establish a collection of prepandemic influenza vaccines which could be used as a basis for vaccine manufacturing in a pandemic situation.

In September of 2003 at an international workshop on pandemic influenza vaccines hosted by the United States National Institutes of Health, a clinical trial plan for pandemic influenza vaccines was developed and levels of priority for evaluation of different influenza candidate vaccine strains were proposed. Influenza H1, H2 and H3 virus subtypes were evaluated as belonging to the "highest priority" level, and influenza viruses of H5, H6, H7 (such as that proposed in this trial), and H9 subtypes were assigned to a "high priority" level. In addition to this, the importance of our proposed trial is supported by WHO's decision to include LAIVs in the WHO global action plan to increase vaccine supply for influenza vaccines.

Prior clinical trials have demonstrated that the Russian monovalent LAIV "Ultragrivac" (manufactured by Microgen) based on 7:1 reassortant of A/duck/Potsdam/1402-6/86 (H5N2) apathogenic avian influenza virus with A/Leningrad/134/17/57 (H2N2) master donor virus was well-tolerated and immunogenic in healthy adult volunteers. Results showed that the vaccine was minimally reactogenic, safe and genetically stable. The seroconversion rate after two doses of the vaccine, defined by a four-fold rise in HAI titre, was approximately 50%. Based on these promising results, WHO stated that avian-human reassortants with the Leningrad 17 strain deserve additional study.

Also of importance is that the Russian LAIV, based on a 6:2 reassortant of A/PR/8/34 (H1N1) with the master donor strain, has been shown in studies in mice to induce not only humoral responses, but also cellular immune responses at the initial site of infection, including CD4+, CD8+ and CD19+ responses.

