### **3.2.2 Secondary Outcome Measures**

Immune responses will be parameterized as the proportion of subjects with at least a four-fold rise after each dose from baseline or as the mean titer after each dose in any of the following:

- Serum hemagglutination inhibition (HAI) antibodies
- Serum neutralizing antibodies
- Serum immunoglobulin class A (IgA) or immunoglobulin class G (IgG) antibodies measured by enzyme-linked immunoassay (EIA)
- Mucosal IgA antibodies in nasal wick specimen

Virus shedding will be parameterized as the proportion of subjects shedding virus [detected by real-time reverse transcriptase polymerase chain reaction (rRT-PCR) in nasal or conjunctival swabs or by isolation in chicken embryos] at any time-point. Shedding data will be reported for every subject at every measured time-point. Molecular characterization of any isolated shed virus will be reported with sequence details of any loss of attenuation mutations.

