## Step 2. Neutralization assay procedure

Tested sera will be diluted 10-fold with trypsin-free Eagle medium and heated during 30 min at temperature 56°C. Two-fold serial dilutions of heated sera in Eagle medium will be prepared in 100 µl aliquots (1:20-1:1280). In addition, virus working dilution (VWD) containing 100 TID50 in 50 µl of Eagle medium supplemented with TPCK-trypsin in concentration of 4 µg/µl will be prepared. Equal volumes of serum dilutions ranging from 1:10 to 1:1280 and VWD will be mixed. Obtained mixtures will be incubated over 1 h at 37°C and then added in amount of 100 µl into each well coated with monolayer of preliminary washed MDCK cells. A total of 50 µl of Eagle medium supplemented with TPCK-trypsin (2 µg/µl) will be added previously into each well.

The following control tests should be performed for each plate:

1. CC- 4 wells coated with cell monolayer containing 150 µg of virus-free Eagle medium supplemented with TPCK-trypsin (2 µg/µl).
2. Virus dose control (VDC). Determination will be performed by repeated titration of VWD in initial condition and in dilutions 10^-1, 10^-2, 10^-3. VWD dilutions will be dispensed in 50 µl per well into 2 rows of wells with addition of 100 µl of Eagle medium supplemented with TPCK-trypsin (2 µg/µl).
3. Serum control (SC). Each of tested sera in dilution of 1/10 (50 µl) will be dispensed into wells containing cell monolayer with addition of 100 µl of Eagle medium (virus-free).

Plates will be incubated in CO2 incubator at temperature (36 ± 0,5)°C during 48 h. Medium will be completely removed, monolayer will be fixed with 80% cold acetone over 15-20 min, and ELISA will be performed as indicated in Step 1.

---

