### Step 3. Data analysis

Neutralizing antibody titer is defined as the last serum dilution when OD450 value is lower than cut-off value (CV) determined according to the following formula:

$$CV = \frac{VWD \text{ OD450} - CC \text{ OD450} + CC \text{ OD450} + KK}{2}, \text{ where}$$

VWD OD450 - OD450 mid-value in control wells containing virus working dilution, CC OD450 - OD450 mid-value in control wells containing non-infected cell culture

Four-fold and greater increase of antibody titers in convalescent sera in comparison with a serum sample obtained during acute illness stage is considered as a diagnostically significant antibody level.

*Notes: When determination of virus dose is correct, positive signal must be registered at VWD dilutions  $10^{-1}$ ,  $10^{-2}$  and be missing at dilution  $10^{-3}$ .*

*In case virus dose control fails to confirm 100 TID50 of virus dose, the test will be repeated.*

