### **11.3.2 Immunogenicity**

Immune responses will be parameterized as the proportion of subjects with at least a four-fold rise after each dose from baseline or as the mean titer after each dose in any of the following:

- Serum hemagglutination inhibition (HAI) antibodies
- Serum neutralizing antibodies using microneutralization assay
- Serum IgA and IgG by EIA
- Mucosal IgA antibodies in nasal wick specimen

Virus shedding will be parameterized as the proportion of subjects shedding virus (detected by real-time reverse transcriptase polymerase chain reaction (rRT-PCR) in nasal or conjunctival swabs or by isolation in chicken embryos) at any time-point. Shedding data will be reported for every subject at every measured time-point.

Percentages of subjects with each immune response will be calculated along with 95% CIs using exact statistical methods. Geometric mean titers (GMTs) along with 95% CIs will also be calculated using the t-test. No multiplicity adjustment to the error rate, alpha, will be made because there are no statistical hypotheses and all analyses of immunogenicity will be descriptive. It is not expected that any subject will have measureable baseline titers to H7. Thus, no screening will be done based on serologic status. However, during analysis, any subject with baseline titer to H7 of >1:20 may be excluded from the immunogenicity analysis or the immunogenicity analysis will be stratified.

Cellular immune responses (cytokine and T-cell) will also be measured using isolated PBMCs tested by flow cytometry and/or ELISPOT assay. These analyses will be exploratory and descriptive only.

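### Seroconversion means at least a four-fold rise in the outcome and analysis sections but a rise above four-fold in the HAI and microneutralization sections; on doubling dilutions the second rule requires eight-fold

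*Protocol*

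**What the plan says.** Two rules stand in the current text.

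**At least four-fold.**
- Section 3.2.2 (secondary outcomes) defines the immune response as the "proportion of subjects with at least a four-fold rise after each dose from baseline or as the mean titer after each dose" and lists HAI and neutralizing antibody under it.
- Section 11.3.2 (immunogenicity analysis) repeats the rule for the same assays: "proportion of subjects with at least a four-fold rise after each dose from baseline".
- Section 8.2.2.3 (nasal IgA by EIA) says "4-fold and greater increase in influenza antibody titer", and section 8.2.2.4 (serum IgA and IgG by EIA) uses the same criterion.
- Step 3 of the microneutralization procedure refers to "Four-fold and greater increase of antibody titers in convalescent sera", although in the language of diagnosing acute illness.

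**Above four-fold.**
- Section 8.2.2.5 (HAI) defines the seroconversion level as the "percent of volunteers showing higher than 4-fold increase of antibody titer in comparison with initial values".
- Section 8.2.2.6 (microneutralization) has the identical criterion.

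On the dilution scheme, section 8.2.2.5 states that "serum specimens are then serially diluted with doubling dilutions", and Step 2 of the microneutralization procedure states that "Two-fold serial dilutions of heated sera in Eagle medium will be prepared". Section 2.1 reports earlier avian LAIV candidates by seroconversion "defined by a four-fold rise in HAI titre".

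**The concern.** On a continuous scale the difference between at least four-fold and more than four-fold would be negligible. On a doubling-dilution scale it is a whole dilution step, and a four-fold rise, exactly two steps, is a common result.

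Three things are at stake:

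- The HAI and microneutralization seroconversion rates depend on which section the analyst follows.
- Under the strict rule these two assays are held to a higher threshold than the EIA measures in the same subjects. Serum or mucosal IgA could then look the more sensitive marker because of the definition alone. Section 2.1 already describes serum IgA as the most consistent response in earlier studies, so that reading would be easy to accept.
- A rate computed under the strict rule could not be set beside the rates in section 2.1, which are reported on a four-fold definition, and would look low against them.

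**Working it through.** The protocol states no expected seroconversion rate and calculates no sample size (section 11.1), so there is no planned figure to reproduce.

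**Inputs from the protocol**
- Vaccine arm: 9 + 21 = 30; placebo arm: 3 + 7 = 10 (section 4).
- Two-fold serum dilutions in both assays (section 8.2.2.5; microneutralization Step 2).
- The neutralizing titre is the last serum dilution below the optical-density cut-off (Step 3), so it is a value on the dilution grid. The Reed-Muench calculation in Step 1 concerns the virus titre, not the serum titre.
- Rates to start from, both after two doses: about 50% for the H5N2 LAIV on the same donor strain, and 92% for another H7N3 LAIV candidate (section 2.1).
- Exact 95% confidence intervals for proportions (section 11.3.2).

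**Input assumed**
- Standard deviation σ of the log2 titre rise, 1 to 2 dilution steps, with a normal shape. The protocol gives neither.

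**Step 1: what the strict rule means.** With one endpoint titre per serum, the ratio of two titres is a power of two: 1, 2, 4, 8, 16 and so on. The smallest ratio above 4 is 8. In dilution steps, the at-least rule needs 2 or more and the strict rule needs 3 or more. The rules differ by exactly those subjects who rise two steps.

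**Step 2: how many subjects that could be.** Let the underlying log2 rise be normal with mean μ and SD σ, and round it to whole steps.

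- P(at least 4-fold) = P(rise ≥ 1.5 steps) = p, so μ = 1.5 + σ·z(p), where z(p) is the standard normal quantile of p.
- P(at least 8-fold) = P(rise ≥ 2.5 steps) = 1 − Φ((2.5 − μ)/σ) = Φ(z(p) − 1/σ).

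For p = 0.50, z = 0:
- σ = 1: Φ(−1) = 0.159
- σ = 1.5: Φ(−0.667) = 0.252
- σ = 2: Φ(−0.5) = 0.309

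For p = 0.92, z = 1.405:
- σ = 1: Φ(0.405) = 0.657
- σ = 1.5: Φ(0.738) = 0.770
- σ = 2: Φ(0.905) = 0.817

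| Rate, at least 4-fold | σ = 1 | σ = 1.5 | σ = 2 |
|---|---|---|---|
| 50% | 16% | 25% | 31% |
| 92% | 66% | 77% | 82% |

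As a share of the starting rate, the strict rule keeps 0.32, 0.50 and 0.62 in the first row and 0.71, 0.84 and 0.89 in the second.

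**Step 3: in subjects.** With 30 vaccinees, 50% is 15 responders. Under the strict rule the expected number is 30 × 0.159 = 4.8, 30 × 0.252 = 7.6 or 30 × 0.309 = 9.3. In the middle case the report would read either 15/30 = 50% (exact 95% CI 31% to 69%) or about 8/30 = 27% (12% to 46%), from the same sera.

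**The case against.** The conflict itself is hard to dispute; the case against concerns its weight.

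- **Place in the protocol.** The sections that define the outcome (3.2.2) and its analysis (11.3.2) agree with each other, and the strict wording sits in laboratory-method sections. A reader would probably follow 3.2.2 and 11.3.2. But the strict wording appears in 8.2.2.5 and 8.2.2.6 as the criterion for evaluating immunogenicity, and nothing ranks the sections.
- **Descriptive and recoverable.** No hypothesis is tested and no sample size or error rate depends on the endpoint. Titres are recorded either way, so both rates remain computable. This stands, and it limits the damage. In a descriptive trial, however, the estimate is the result, and choosing the rule after seeing both rates would be data-dependent.
- **A later analysis plan.** Section 11.3 provides for a data analysis plan before the database freeze and before the statistician is unblinded. That is the last point at which to settle the rule, but a plan following either protocol rule would contradict the other.
- **Size.** Halving rests on an assumed spread. It occurs from a 50% starting rate with σ up to about 1.5. From 92%, the loss at σ between 1 and 2 is about 11% to 29% of the rate. The normal model may also not fit: section 11.3.2 expects no measurable baseline titres, so rises start from the assay floor, and a mixture of clear responders and non-responders could lose fewer subjects. This stands for the magnitude and leaves the contradiction untouched.
- **Microneutralization is not uniformly strict.** Step 3 uses the at-least wording. That is correct; it means the assay's own text is divided, and it suggests which wording was intended.
- **Comparison with earlier vaccines.** No formal comparison is planned. That also stands, although section 2.1 supplies the rates a reader will naturally use.

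**Conclusion.** The concern holds. The protocol fixes two incompatible responder rules for HAI and neutralizing antibody, and on doubling dilutions the stricter one is an eight-fold rule. That conclusion follows from the text and assumes only one endpoint titre per serum; averaging replicate titres could give intermediate ratios, but the protocol describes no replicate testing of sera.

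The numerical effect depends on the assumed distribution: the strict rule may halve the rate or worse when about half the vaccinees reach four-fold, with a smaller relative loss when nearly all do. The consequence is confined to a descriptive secondary outcome, but there it changes the headline rate and its comparability with the EIA results and the earlier vaccines.

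**What to change.** In the seroconversion criteria of sections 8.2.2.5 and 8.2.2.6, replace the strict wording with at least 4-fold, matching sections 3.2.2, 11.3.2, 8.2.2.3, 8.2.2.4 and microneutralization Step 3. Add that the rule applies to the ratio of the reported post-dose titre to the reported baseline titre. Make the change before unblinding.

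The cost is a few words in two sections, with no effect on data collection, specimens or participants.

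The same two criterion lists should be read through at the same time. Their 1:40 titre criterion is also a strict inequality on a doubling grid, and they refer to Day 21, whereas both sections collect serum on Days 0, 28 and 56.

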#### **8.2.2.6 Serum Antibody to Influenza Virus Detected by Microneutralization Assay**

The microneutralization assay is an alternative test for determining immunologic response to vaccination. Serum, along with live influenza virus, is added to a culture of Madin-Darby Canine Kidney (MDCK) cells. Titers of neutralizing antibodies are expressed as an amount of the greatest dilution giving a neutralization of 50% of tissue cytopathic effects of the virus in the tissue culture (TCID50). Serum specimens will be tested for the presence of neutralizing antibodies to influenza by microneutralization by IEM.

Vaccine immunogenicity will be evaluated due to the following criteria:

1. Seroconversion factor – increase of antibody geometric mean titers (GMT) on Day 21 in comparison with initial antibody levels in terms of "fold" increase.
2. Seroconversion level – percent of volunteers showing higher than 4-fold increase of antibody titer in comparison with initial values.
3. Seroprotection level – percent of volunteers showing antibody titer exceeding 1:40 on Day 21 post-vaccination.

For these assays, serum specimen collection will occur on Days 0, 28 and 56. Collection must prior to administration of study vaccine or placebo on Days 0 and 28.

